
#### Recruitment

2.5.10

Patients are recruited through participating rehabilitation clinics that specialize in treating PCS. Patients receive information about the study either in advance by post or upon admission to the clinic. During the admission interview, a therapist or physician establishes whether the inclusion and exclusion criteria are met, and asks patients if they wish to participate in PoCo-FRAME. The three groups (two interventions and one control) are recruited in clusters, with a two-week washout phase in each of the two rehabilitation clinics. This means that only one group is recruited and examined at a time, until that group is complete. This reduces confounding factors, such as disappointed patients in the control group talking to patients in an intervention group.

### Assignment of interventions: sequential cohort design

2.6

In order to recruit enough patients within a reasonable timeframe, the study will be conducted at two locations. Due to different treatment concepts at each rehabilitation clinic, this will also increase the study’s external validity. Patients will be recruited into the two intervention groups and the control group in clusters, with a wash-out phase in each clinic. This means that only one group will be recruited and examined at a time, and the next group will only be recruited two weeks after the previous group has been fully discharged. This reduces confounding factors, such as disappointed patients in the control group talking to patients in an intervention group. The random allocation of patients is based on their start date on the rehabilitation program.

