#### Explanation for the choice of comparators

2.5.1

Throughout the study, all three study groups participate in regular psychosomatic rehabilitation and receive treatment as usual (TAU) in accordance with the guidelines of the German pension insurance for patients with PCS. The control group (group 1) receives only TAU, while the other two groups additionally receive one of the two interventions (group 2 = JOURNAL group; group 3 = FRAME group). Although participants are assigned to groups according to a sequential cohort design, systematic differences or changes in symptom burden should be minimal and attributed to group affiliation and whether a study intervention was received. Which group participants are in depends solely on the timing of their rehabilitation, not on other systematic differences. (see **Figure 1**). Patients are informed about the study on the first day in the rehabilitation hospital. All treating providers are aware of the participants’ condition assignments.

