#### Sample size

2.5.9

A total sample of N = 84 participants will participate in one of three groups: a control group receiving treatment as usual only (TAU), a JOURNAL group, and a FRAME group, with 28 individuals in each group. Case numbers are based on the following facts: In general, hardly any studies have been published on the effectiveness of psychosomatic rehabilitation measures for patients with PCS (42). Initial studies show medium to large effects, depending on the outcome variable. For example, effects were observed for somatoform complaints (d=0.60) and the 6-min walking test (d=1.22) (6). No study could be found that showed effect sizes for changes in earning capacity or ability to work. Rief et al. (26) found a large effect size (approximately d=1.0, calculated from the data in the article) for improvements in limitations and the subjective assessment of ability to work in hours (approximately d=2.0, calculated from the data in the article) through the intervention to optimize expectations in patients undergoing bypass surgery. As the patients in this study are already undergoing psychosomatic rehabilitation treatment, the intervention is an add-on that may not show a statistically large effect (Cohen’s d > 0.8). Therefore, the sample size should be large enough to detect a medium effect. Furthermore, it should be possible to test the effectiveness of each intervention compared to the treatment as usual (TAU) group. For a 2x2 analysis of variance with repeated measures (ANOVA; 2 groups x 2 time points) for the change in the main outcome measure (e.g., WAI) from admission to discharge, with a mean effect size of f=0.25 and a power of 0.95, N = 54 patients are required for the comparison of TAU with one of the intervention groups (calculated with G*Power 3.1.9.6; freeware from Kiel University). In order to compare the second intervention group with the TAU group, further N = 54/2 = 27 patients are required in this group. In total, this equates to N = 81 patients. To be able to divide these patients between the two clinics and the three groups, a total of N = 84 patients are required, for whom at least admission and discharge data are available. This means that the sample is also sufficiently large for 2x3 ANOVAs (2 groups x 3 time points; N = 36 required). In summary, we plan to conduct two 2×2 ANOVAs, specifically using a mixed-design ANOVA (two-factor ANOVA with one repeated-measures factor and one between-group factor). With an estimated drop-out rate of 20%, 100 patients must be recruited.

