#### Statistical methods for primary and secondary outcomes

2.8.1

Demographic data will be used to describe study participants and reported as means and standard deviations or median and interquartile range, where appropriate. The change in primary and secondary outcomes as well as objective measures from the beginning to the end of rehabilitation for each intervention group individually with the control group will be analyzed with 2x2 ANOVAs (2 time points x 2 groups). The longterm effects after six months will also be analyzed for each intervention group with separate 3x2 ANOVAs (3 time points x 2 groups). Since this is the first study involving these interventions in patients with PCS, prior correction will not be used, but will be discussed appropriately in the publication of the results. For the exploratory evaluation of personality measures, we plan to calculate predictor analyses, such as regression analyses to predict changes in primary and secondary outcomes.

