#### Methods in analysis to handle protocol non-adherence and any statistical methods to handle missing data

2.8.2

Study adherence is defined as participation in all sessions according to group assignment and completion of at least 80% of the tasks in the booklet. Non-adherence is noted if participants fail to complete more than 20% of the tasks. Therapists use a standardized checklist to document which components were completed or omitted and note the reasons for any deviations (e.g., if the content of the session was too demanding). Adherence is monitored by attendance at sessions, documentation by therapists, and self-reports by patients. Recruitment continues for each group and clinic until the required 14 patients have met the adherence criterion.

The primary outcome, the WAI, must not contain any missing values. All other questionnaires are evaluated in accordance with their manuals, and individual missing values are treated or imputed as described in the manuals.

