#### Composition of the coordinating center and trials steering committee

2.9.1

The study is coordinated by the Department of Psychosomatic Medicine and Psychotherapy in Ulm. Statistical analyses are carried out at this department and at the Institute for Rehabilitation Medicine in Bad Buchau. The psychotherapeutic interventions will take place at the psychosomatic rehabilitation clinics Glotterbad and Schlossklinik Bad Buchau in Germany. At each study site, 42 participants will be included. The coordination team meets regularly once a week. Full staff meetings are held monthly.

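### The primary ANOVA and its 0.95 power assume independent patients although condition is assigned to whole clinic-by-period blocks; if WAI change correlates within blocks, the primary tests are too liberal

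*Protocol article*

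**What the plan says.** **Allocation.** Section 2.6 sets out how patients enter the arms: "Patients will be recruited into the two intervention groups and the control group in clusters, with a wash-out phase in each clinic". It spells out the consequence for each clinic: "only one group will be recruited and examined at a time". A later group opens two weeks after its predecessor has left the clinic. Section 2.5.1 adds: "Which group participants are in depends solely on the timing of their rehabilitation, not on other systematic differences". Section 2.3 calls the design non-randomized.

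**Block size.** Section 2.8.2: "Recruitment continues for each group and clinic until the required 14 patients have met the adherence criterion". Section 2.9.1: "At each study site, 42 participants will be included". Section 2.5.9 plans 84 patients, "with 28 individuals in each group". These agree: 3 groups x 14 = 42 per clinic, and 2 clinics x 14 = 28 per arm.

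**Analysis.** Section 2.8.1 says that the change "for each intervention group individually with the control group will be analyzed with 2x2 ANOVAs (2 time points x 2 groups"). Section 2.5.9 specifies a mixed design with one repeated-measures factor and one between-group factor. Neither section names a clinic, period, block or therapist term.

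**Power.** Section 2.5.9, on each pairwise contrast between TAU and an intervention arm: "with a mean effect size of f=0.25 and a power of 0.95, N = 54 patients are required for the comparison of TAU with one". No design effect or ICC appears. The two clinics enter only where 81 is rounded up to 84.

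**The concern.** The unit that receives a condition is a clinic-by-period block, not a patient. Each primary contrast has four such units, two per arm. The mixed ANOVA models correlation between one patient's two measurements but counts all 56 patients as independent between-patient information (54 error degrees of freedom).

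Patients in one block share the programme and conditions of that clinic during those months. If their WAI changes are therefore somewhat alike, an arm mean varies more than the ANOVA assumes. Both primary p-values and intervals would then claim too much precision, and the stated 0.95 would overstate the power of a test that keeps its 5% level. A positive WAI result could be ordinary block-to-block variation, and the planned error bars would not show it. Section 2.8.1 applies no multiplicity correction, so nothing else in the plan absorbs excess error.

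This concerns the standard error. Confounding of arm with calendar time is a separate matter of bias.

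**Working it through.** **Inputs from the protocol.** f = 0.25, power 0.95, N = 54 per comparison, 28 per arm (2.5.9); 14 per group and clinic (2.8.2); two clinics (2.2).

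**Inputs assumed.** Alpha 0.05 and pre-post correlation 0.5. Neither is stated, but together they reproduce N = 54; correlations of 0, 0.3 and 0.7 would give 106, 76 and 34. The within-block ICC of WAI change is not given either, so a range from 0 to 0.10 is shown.

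**Step 1: reproduce the plan's figure.** For the group-by-time interaction, lambda = f² x N x 2/(1 − 0.5), with 1 and N − 2 degrees of freedom.
- N = 54: lambda = 0.0625 x 54 x 4 = 13.5, power 0.950. The plan's figure is reproduced, under independence.
- N = 56: lambda = 14.0, power 0.957.

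**Step 2: design effect.** With m = 14 per block, DE = 1 + 13 x ICC. The standard error of the contrast grows by √DE, effective n per arm is 28/DE, and lambda becomes 14/DE. At ICC 0.05, DE = 1.65, √DE = 1.28, effective n = 17.0 and lambda = 8.48.

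**Step 3: type I error of the planned test.** WAI change was simulated (200,000 trials per setting) for 2 arms x 2 clinics x 14 patients with a random clinic-by-period effect. The t-test on change was used, which is equivalent to the interaction F. Analytic check at ICC 0.05: 2 x (1 − Φ(1.96/√1.65)) = 0.127.

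| Assumed ICC | DE | √DE | Effective n per arm | Type I error at nominal 5% | Power at f = 0.25, N = 56, lambda/DE |
|---|---|---|---|---|---|
| 0 | 1.00 | 1.00 | 28.0 | 0.048 | 0.957 |
| 0.01 | 1.13 | 1.06 | 24.8 | 0.065 | 0.933 |
| 0.02 | 1.26 | 1.12 | 22.2 | 0.081 | 0.905 |
| 0.05 | 1.65 | 1.28 | 17.0 | 0.129 | 0.816 |
| 0.10 | 2.30 | 1.52 | 12.2 | 0.203 | 0.678 |

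The power column is for a test corrected with a known ICC.

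**Step 4: do stable clinic differences matter?** No. Each clinic supplies all three arms, so they cancel in the contrast. Adding a stable clinic variance of 0.05 gives a type I error of 0.048 at block ICC 0 and 0.125 at block ICC 0.05. Nor does a clinic term cure the problem: with one in the model, the type I error at ICC 0.05 is 0.129. Only variation between periods within a clinic does harm.

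**Step 5: can the data supply the correction?** Hardly. An analysis of the four block means has 2 degrees of freedom. It holds its level but has power of only 0.52 at ICC 0 and 0.37 at ICC 0.05. Random block effects or sandwich errors face the same shortage of blocks.

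**The case against.** The strongest objection is that the harm is conditional. A reader might infer that the primary standard error is certainly too small. The protocol does not support this: it gives no ICC, the test holds its level at ICC 0, and the error is only about 6.5% at ICC 0.01. The larger figures rest on assumed values. This objection stands and limits the conclusion. Equally, the protocol offers no ground for zero beyond the expectation in 2.5.1 that systematic differences will be minimal.

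Other tempting readings also go too far:
- *Shared clinic staff and treatment concepts drive the problem.* Where stable, they are common to all arms and cancel.
- *A handful of FRAME therapists drives it.* No number of therapists is given, and 3.1 leaves open whether patients' own therapists deliver the sessions.
- *Fellow patients make the ICC large.* Recruitment runs for about a year (2.10), so three successive groups take about 12/3 = 4 months each, with stays of 3 to 4 weeks. Many patients in a block would never meet. FRAME is individual therapy, and JOURNAL is done largely alone. This argues against a large ICC but does not exclude a positive one.
- *Season is part of this variance.* If both clinics run the arms in the same order, season is common to both blocks of an arm. It is then bias, which no ICC correction addresses. The text does not state the order, and Figure 1 is not shown.

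The article also calls the study a proof of principle with preliminary results (3.1). That softens the consequence of a liberal p-value, but the hypotheses in the Introduction still claim significantly greater improvement. A statistical analysis plan that is not shown may contain a clustering sensitivity analysis; the article itself nevertheless commits to a specific model and a power figure, both of which assume independence.

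**Conclusion.** The point holds in conditional form. The block structure and the independence assumption both stand in the protocol, and N = 54 at power 0.95 is reproduced only under independence. If WAI change is positively correlated within clinic-by-period blocks, the primary standard errors are too small and the tests too liberal. For ICC 0.01 to 0.10, the type I error is about 6.5% to 20% and power at f = 0.25 falls from about 0.93 to 0.68. Direction follows from the design once the ICC is positive; size depends on an ICC that the protocol does not give.

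The figures also assume alpha 0.05, pre-post correlation 0.5 and exactly 14 analysed per block. Larger blocks would raise the design effect: if all 100 recruited patients were analysed, m = 100/6 = 16.7 and DE at ICC 0.05 would be 1 + 15.7 x 0.05 = 1.78.

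**What to change.** 1. **Section 2.5.9:** state that the 0.95 power assumes no within-block correlation, and give power over the range: about 0.93, 0.91, 0.82 and 0.68 at ICC 0.01, 0.02, 0.05 and 0.10 with 56 patients at f = 0.25.
2. **Section 2.8.1:** report each primary WAI contrast also with its standard error multiplied by √(1 + (m − 1) x ICC) over ICC 0.01 to 0.10, where m is the number actually analysed per block. The factor is approximate: at ICC 0.05 the simulated ratio of true to model standard error is 0.343/0.263 = 1.30, against 1.28 from the formula. Show the TAU-versus-intervention difference separately for each clinic.
3. **Interpretation:** if an interval includes zero within that range, say that the effect cannot be separated from block-to-block variation.

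No single ICC should become a pass/fail rule, because no value has a source in the protocol. Random block effects or sandwich errors should not be relied on with four blocks per contrast. These changes do not address calendar effects common to both clinics.

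The cost is wording in two sections and a few lines of code, with no extra patients, visits or data. The downside is a less favourable stated power and wider sensitivity intervals.

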**Methods:**

The study implements a 3-arm, parallel group, longitudinal non-randomized controlled, sequential cohort design. The trial is designed to estimate the effect of *1) a 3-session psychotherapeutic expectation-focused integrative, manualized intervention, and 2) a brief intervention where patients are asked to write down their expectations on their own in a journal, compared to 3) a treatment-as-usual-only control condition (usual treatment in rehabilitation, no study intervention)*. Since the predominant symptoms in PCS patients vary a lot, the Work Ability Index (WAI) is considered as a proxy for earning capacity as primary outcomes.

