### Design

2.3

The multicenter, longitudinal, quantitative trial employs a quasi-experimental, non-randomized sequential cohort design with three arms in a real-life design. The entire project will run from January 01, 2024, until expected June 30, 2027.

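### Allocation by admission date is called random in a non-randomized design, and differences are credited to group although group and calendar period coincide within each clinic

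*Protocol article*

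**What the plan says.** All references are to the protocol article.

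- **Design label.** The abstract describes a "longitudinal non-randomized controlled, sequential cohort design". Section 2.3 says the trial "employs a quasi-experimental, non-randomized sequential cohort design with three arms".
- **Allocation.** Section 2.6 says: "The random allocation of patients is based on their start date on the rehabilitation program".
- **Recruitment order.** Section 2.5.10, on each of the two clinics: "This means that only one group is recruited and examined at a time, until that group is complete". Section 2.6 repeats this: "only one group will be recruited and examined at a time, and the next group will only be recruited two weeks after the previous group". The two weeks run from the discharge of that group's last patient. The stated purpose of the gap is to limit contact between patients of different groups.
- **Comparability.** Section 2.5.1 says that "systematic differences or changes in symptom burden should be minimal and attributed to group affiliation" and to receipt of a study intervention. It continues: "Which group participants are in depends solely on the timing of their rehabilitation, not on other systematic differences". It adds that all treating providers know which condition a participant is in.
- **Enrolment.** Under section 2.5.10, a clinic therapist or physician checks eligibility at admission and invites the patient.
- **Analysis.** Sections 2.5.9 and 2.8.1 give 2x2 mixed ANOVAs (time by group) comparing each intervention with usual treatment.

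**The concern.** Two statements about the same allocation cannot both be right. If admission date decides the group and each clinic runs one group at a time, nothing is left to chance.

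The more consequential problem is the inference drawn in section 2.5.1. That group depends only on timing is offered as a reason to expect comparable groups. In a sequential cohort design, timing is itself the systematic difference. Anything that changes over the recruitment year changes together with group. Staff who judge eligibility and invite patients can also know which condition is running, so enrolment may differ between cohorts.

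A difference between cohorts that has nothing to do with the intervention would be read as a treatment effect. Recruiting more patients would not remove it.

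**Working it through.** **1. Is there a chance mechanism?** The abstract and section 2.3 say the study is non-randomized. Section 2.6 says random, but gives its own mechanism, the start date. The text describes no random sequence, no randomized order of the recruitment blocks and no concurrent control. The non-randomized label fits the described conduct; the word random does not.

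**2. Can group be separated from period?** Sections 2.5.10 and 2.6 give three consecutive blocks in each clinic, one group per block. Knowing a patient's clinic and block therefore fixes the group, and no model can estimate a group effect and a block effect separately within a clinic. If the two clinics ran the groups in different orders, a period effect common to both might partly cancel in the pooled comparison. The text does not give the order, and Figure 1 was not available for this check.

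**3. What could move with period?** Section 2.10 places recruitment between summer 2025 and summer 2026, so consecutive blocks can fall in different seasons. Section 2.2 has therapists trained only before the respective intervention group and grants that some influence on standard therapy cannot be excluded. Section 2.5.5 says usual treatment varies between patients. These show that a period shift is possible, not that one occurs.

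**4. Does a planned figure depend on the wording?** Section 2.5.9 states N = 54 for one two-group comparison, with f = 0.25 and power 0.95. Assume alpha = 0.05 and a correlation of 0.5 between time points; neither is stated. With two time points:

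lambda = f² × N × 2 / (1 − 0.5) = 0.0625 × 54 × 2 / 0.5 = 13.5, on 1 and 52 degrees of freedom.

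Power is 0.950, so N = 54 reproduces. Correcting the wording changes no sample-size figure.

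**5. Size of a possible distortion (illustration only).** Take no treatment effect, 28 patients per group (section 2.5.9), and a two-sided 5% t test on WAI change, which is the time-by-group test in a 2x2 design. Let the mean change differ between two cohorts by d SD of change for reasons other than the intervention. The article gives no value for d, so a range is assumed.

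Noncentrality = d / √(2/28) = 3.742 × d, with 28 + 28 − 2 = 54 degrees of freedom.

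| Assumed shift d | Noncentrality | False-positive rate |
|---|---|---|
| 0 | 0 | 5.0% |
| 0.1 | 0.374 | 6.6% |
| 0.2 | 0.748 | 11.4% |
| 0.3 | 1.122 | 19.7% |

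For scale, the effect in step 4 corresponds to √13.5 × √(2/27) = 1.0 SD of change under the same assumptions. These shifts are thus a tenth to three tenths of the effect the sample was sized for.

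**The case against.** The case on the other side has real substance.

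- **The design is labelled correctly in the prominent places.** The abstract, section 2.3 and the heading of section 2.6 all identify a non-randomized or sequential cohort design, and the disputed sentence names its own mechanism. A careful reader would probably not take this for a randomized trial. This stands and limits the harm from the single word.
- **The article is more cautious than one sentence suggests.** A reader might infer that it claims to exclude every systematic difference. It does not: section 2.5.1 says such differences should be minimal, section 2.5.3 grants that selection bias cannot be ruled out, and section 3.1 calls the results preliminary and a later randomized trial desirable. None of these names period confounding, and section 2.5.1 still credits differences to group.
- **Part of section 2.5.1 is right.** That group depends only on timing describes the allocation correctly and should stay.
- **The analysis is not without protection.** A reader might infer that the ANOVAs leave every imbalance in place. The time-by-group test works on change, so stable differences in baseline level are already removed. Clinic is balanced by design: 14 per group and clinic (section 2.8.2) gives 14 × 3 × 2 = 84. Clinic therefore does not confound group.
- **Covariate lists commonly sit in the statistical analysis plan.** That plan is not shown, so the absence of an adjusted model here is not itself an error.
- **Nothing shows that the cohorts differ.** The article does not report that season, referrals, staffing or usual care changed between blocks. Only the possibility stands.

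**Conclusion.** The point holds as an internal contradiction together with an inference the design does not support. Calling the allocation random in section 2.6 conflicts with the abstract and section 2.3. Two clauses in section 2.5.1, the denial of other systematic differences and the attribution of differences to group and intervention, claim what randomization would give and consecutive single-group blocks cannot. The missing limitation is specific: intervention and period are fully confounded within a clinic.

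The size is unknown. The rates of about 6.6%, 11.4% and 19.7% rest on assumed shifts of 0.1, 0.2 and 0.3 SD of change and on 28 analysed patients per group. They show sensitivity and do not estimate actual bias.

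Stronger readings are not supported. The documents do not show that the groups differ, that the stated comparison is biased by any given amount, or that the registry entry, which is not at hand, repeats the wording.

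**What to change.** 1. In section 2.6, describe the mechanism as *non-random allocation by admission date*.
2. In section 2.5.1, keep the statement that group depends only on timing. Withdraw the clause denying other systematic differences and the clause attributing differences to group and receipt of an intervention.
3. In section 3.1, state that intervention and period effects cannot be separated within a clinic.
4. Unless the statistical analysis plan already holds one, pre-specify one sensitivity analysis of WAI change adjusted for a few variables already collected at T1, for example baseline WAI, age, employment and one symptom-severity score. With 28 per group the list should be short. Say plainly that this addresses measured case mix only and cannot remove the effects of season, staffing or changes in usual care.

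The cost is a few sentences and one further model. Conduct, sample size and primary analysis stay as they are; the causal claim becomes more modest.
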